#### **10.4.4. Contraception Methods**

Contraceptive use by men or women should be consistent with local availability/regulations regarding the use of contraceptive methods for those participating in clinical trials.

##### **Highly Effective Methods That Have Low User Dependency**

1. Implantable progestogen only hormone contraception associated with inhibition of ovulation\*.
2. Intrauterine device.
3. Intrauterine hormone -releasing system.
4. Bilateral tubal occlusion.
5. Vasectomized partner.
  - Vasectomized partner is a highly effective contraceptive method provided that the partner is the sole sexual partner of the WOCBP and the absence of sperm has been confirmed. If not, an additional highly effective method of contraception should be used. The spermatogenesis cycle is approximately 90 days.
  - \* not approved in Japan.

##### **Highly Effective Methods That Are User Dependent**

6. Combined (estrogen and progestogen-containing) hormonal contraception associated with inhibition of ovulation.
  - Oral;
  - Intravaginal\*;
  - Transdermal\*;
  - \* not approved in Japan.
7. Progestogen only hormone contraception associated with inhibition of ovulation.

- Oral\*;
  - Injectable\*.
  - not approved in Japan.
8. Sexual abstinence.
- Sexual abstinence is considered a highly effective method only if defined as refraining from heterosexual intercourse during the entire period of risk associated with the study intervention. The reliability of sexual abstinence needs to be evaluated in relation to the duration of the study and the preferred and usual lifestyle of the participant.

One of the following effective barrier methods must be used in addition to the highly effective methods listed above that are user dependent:

- Male or female\* condom with or without spermicide;
- Cervical cap\*, diaphragm\*, or sponge with spermicide\*;
- A combination of male condom with either cervical cap\*, diaphragm\*, or sponge with spermicide\* (double-barrier methods).
- \* not approved in Japan.

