- i) **Contraception Check:** The investigator or his or her designee, in consultation with the participant, will confirm that the participant has selected an appropriate method of contraception for the individual participant (and his or her partner[s]) from the permitted list of contraception methods and will confirm that the participant has been instructed in its consistent and correct use. The investigator or designee will inform the participant of the need to use highly effective contraception consistently and correctly and document the conversation and the participant's affirmation in the participant's chart (participants need to affirm their consistent and correct use of at least 1 of the selected methods of contraception). In addition, the investigator or designee will instruct the participant to call immediately if the selected contraception method is discontinued or if pregnancy is known or suspected in the participant or partner.
- j) **Concomitant Treatments:** All concomitant medications and nondrug supportive interventions should be recorded on the CRF.
- k) **Hematology, Blood Chemistry, Coagulation, and Urinalysis:** No need to repeat on C1D1 if baseline assessment is performed within 7 days prior to that date ([Section 10.2](#) for a complete list of clinical laboratory tests).
- l) **Pregnancy Test:** Pregnancy tests may be urine or serum tests, but must have a sensitivity of at least 25 mIU/mL. Pregnancy tests will be performed in WOCBP. Following a negative pregnancy test result at screening, appropriate contraception must be commenced and a second negative pregnancy test result will be required at the baseline visit prior to the participant's receiving the study intervention. Pregnancy tests will also be done whenever 1 menstrual cycle is missed during the active treatment period (or when potential pregnancy is otherwise suspected) and at the end of the study. Pregnancy tests may also be repeated if requested by IRBs/ECs or if required by local regulations (see [Section 10.2](#)).
- m) **PSA:** For prostate cancer only, PSA to be performed every 4 weeks from C1D1 (±2 days) until EOT.
- n) **Viral Disease Screening Tests:** HBsAg, , HBcAb, anti-HBs, HCVAb, and HIV to be conducted by local laboratory where required by local regulations or if warranted by participant history.
- o) **Registration:** Participant enrollment number and dose level allocation assigned by Pfizer Inc.

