**3. Part 2 (Dose Expansion) tumor indications and prior lines of therapy**

- **Part 2A (ER+HER2- breast cancer 2L+, monotherapy):** Histological or cytological diagnosis of locally advanced or metastatic ER+HER2- breast cancer. Participants must have progressed after at least 1 prior line of CDK4/6 inhibitor and at least 1 prior line of endocrine therapy. Additional Korea specific requirements are provided in [Appendix 8 \(Section 10.8.3\)](#).
- **Part 2B (ER+HER2- breast cancer 2-4L, combination with fulvestrant):**
  - Histological or cytological diagnosis of advanced or metastatic ER+HER2- breast cancer. Participants must have progressive disease after at least 1 prior line of a CDK4/6 inhibitor and at least 1 prior line of endocrine therapy.
  - Participants must not have received more than 3 prior lines of systemic therapies including up to 1 line of cytotoxic chemotherapy for visceral disease in advanced or metastatic setting; Participants may have but are not required to have prior treatment with fulvestrant.

- [REDACTED]

[REDACTED]

[REDACTED]

4. Participants with ER+HER2- advanced or metastatic breast cancer must have documentation of ER-positive tumor ( $\geq 1\%$  positive stained cells) based on most recent tumor biopsy (unless non-measurable disease where most recent documentation will be provided) utilizing an assay consistent with local standards.

5. Participants with ER+HER2- advanced or metastatic breast cancer must have documentation of HER2-negative tumor: HER2-negative tumor is determined as immunohistochemistry score 0/1+ or negative *by in situ* hybridization (FISH/CISH/SISH/DISH) defined as a HER2/CEP17 ratio <2 or for single probe assessment a HER2 copy number <4.
6. Female participants with ER+HER2- advanced or metastatic breast cancer considered to be of childbearing potential (or have tubal ligations only) must be willing to undergo medically induced menopause by treatment with the approved LHRH agonist such as goserelin, leuprolide or equivalent agents to induce chemical menopause.
7. Female participants with ER+HER2- advanced or metastatic breast cancer of nonchildbearing potential must meet at least 1 of the following criteria of achieving postmenopausal status, defined as follows:

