  - Cessation of regular menses for at least 12 consecutive months with no alternative pathological or physiological cause; [status may be confirmed with/and have] a serum follicle-stimulating hormone (FSH) level confirming the post menopausal state;
  - Have undergone a documented hysterectomy and/or bilateral oophorectomy;
  - Have medically confirmed ovarian failure. All other female participants (including female participants with tubal ligations) are considered to be of childbearing potential.
8. Participants must have at least 1 measurable lesion as defined by RECIST version 1.1 that has not been previously irradiated.
9. ECOG Performance Status PS 0 or 1 (See [Appendix 12: Section 10.12](#)).
10. Adequate Bone Marrow Function, including:
  - a. ANC  $\geq 1,500/\text{mm}^3$  or  $\geq 1.5 \times 10^9/\text{L}$ ;
  - b. Platelets  $\geq 100,000/\text{mm}^3$  or  $\geq 100 \times 10^9/\text{L}$ ;
  - c. Hemoglobin  $\geq 9 \text{ g/dL}$ .
11. Adequate Renal Function, including:
  - a. Serum creatinine  $\leq 1.5 \times \text{ULN}$  or estimated creatinine clearance GFR  $\geq 60 \text{ mL/min}$  ( $\geq 50 \text{ mL/min}$  for Part 2 dose expansion is acceptable) as calculated using the method standard for the institution. In equivocal cases, a 24 hour urine collection test can be used to estimate the creatinine clearance more accurately.

12. Adequate Liver Function, including:

- a. Total serum bilirubin  $\leq 1.5 \times$  ULN unless the participant has documented Gilbert syndrome;
  - b. AST and ALT  $\leq 2.5 \times$  ULN; AST and ALT  $\leq 3.0 \times$  ULN if there is liver involvement by the tumor for Part 1 dose escalation. AST and ALT  $\leq 5.0 \times$  ULN if there is liver involvement by the tumor for Part 2 dose expansion.
13. Resolved acute effects of any prior therapy to baseline severity or CTCAE Grade  $\leq 1$  except for AEs not constituting a safety risk by investigator judgment.
14. Participants who are willing and able to comply with all scheduled visits, treatment plan, laboratory tests, lifestyle considerations, and other study procedures.
15. Capable of giving signed informed consent as described in [Section 10.1.3](#), which includes compliance with the requirements and restrictions listed in the ICD and in this protocol.

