### 5.3.2. Contraception

The investigator or his or her designee, in consultation with the participant, will confirm that the participant has selected an appropriate method of contraception for the individual participant and his or her partner(s) from the permitted list of contraception methods (see [Appendix 4: Section 10.4.4](#)) and will confirm that the participant has been instructed in its consistent and correct use. At time points indicated in the [SoA](#), the investigator or designee will inform the participant of the need to use highly effective contraception consistently and correctly and document the conversation and the participant's affirmation in the participant's chart (participants need to affirm their consistent and correct use of at least 1 of the selected methods of contraception). In addition, the investigator or designee will instruct the participant to call immediately if the selected contraception method is discontinued or if pregnancy is known or suspected in the participant or partner.

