### 10.4.2. Female Participant Reproductive Inclusion Criteria

- A female participant is eligible to participate if she is not pregnant or breastfeeding (women who are currently breastfeeding and intend to interrupt breastfeeding are excluded from participating), and at least 1 of the following conditions applies:
- Is not a WOCBP (see definitions below in [Section 10.4.3](#)).

OR

- Is a WOCBP and using a contraceptive method that is highly effective (with a failure rate of <1% per year), preferably with low user dependency, as described below during the intervention period and for at least 28 days after the last dose of study intervention, which corresponds to the time needed to eliminate any reproductive safety risk of the study intervention(s). The investigator should evaluate the effectiveness of the contraceptive method in relationship to the first dose of study intervention.
- Is a WOCBP and using a contraceptive method that is highly effective (with a failure rate of <1% per year), with high user dependency, as described below during the intervention period and for at least 28 days after the last dose of study intervention, which corresponds to the time needed to eliminate any reproductive safety risk of the

study intervention(s). In addition, a second effective method of contraception, as described below, must be used. The investigator should evaluate the effectiveness of the contraceptive method in relationship to the first dose of study intervention.

- A WOCBP agrees not to donate eggs (ova, oocytes) for the purpose of reproduction during this period. The investigator should evaluate the effectiveness of the contraceptive method in relationship to the first dose of study intervention.
- The investigator is responsible for review of medical history, menstrual history, and recent sexual activity to decrease the risk for inclusion of a woman with an early undetected pregnancy.

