#### **10.4.3. Woman of Childbearing Potential**

A woman is considered fertile following menarche and until becoming postmenopausal unless permanently sterile (see below).

If fertility is unclear (eg, amenorrhea in adolescents or athletes) and a menstrual cycle cannot be confirmed before the first dose of study intervention, additional evaluation should be considered.

Women in the following categories are not considered WOCBP:

1. Premenopausal female with 1 of the following:
  - Documented hysterectomy;
  - Documented bilateral salpingectomy;
  - Documented bilateral oophorectomy.

For individuals with permanent infertility due to an alternate medical cause other than the above, (eg, mullerian agenesis, androgen insensitivity), investigator discretion should be applied to determining study entry.

Note: Documentation for any of the above categories can come from the site personnel's review of the participant's medical records, medical examination, or medical history interview. The method of documentation should be recorded in the participant's medical record for the study.

2. Postmenopausal female.
  - A postmenopausal state is defined as no menses for 12 months without an alternative medical cause. In addition, a
  - High FSH level in the postmenopausal range must be used to confirm a postmenopausal state in women under 60 years old and not using hormonal

contraception or HRT. When there is a high FSH level, it should be confirmed that there is no other medical cause.

- Female on HRT and whose menopausal status is in doubt will be required to use one of the non-estrogen hormonal highly effective contraception methods if they wish to continue their HRT during the study. Otherwise, they must discontinue HRT to allow confirmation of postmenopausal status before study enrollment.

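### Protocol 10.4.4 lists combined oestrogen-progestogen contraception for any woman of childbearing potential, with no exception for ER+ breast cancer

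*Protocol*

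**What the plan says.** All references are to the protocol.

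- **Inclusion 6 (5.1)** covers ER+HER2- women of childbearing potential, including those with tubal ligation only. Each "must be willing to undergo medically induced menopause by treatment with the approved LHRH agonist".
- **Inclusion 7 (5.1)** sets out how an ER+ woman qualifies as postmenopausal and then closes the class: "All other female participants (including female participants with tubal ligations) are considered to be of childbearing potential".
- **10.4.2** admits a woman of childbearing potential (WOCBP) who uses a highly effective method. It prefers low user dependency but also accepts the alternative: "Is a WOCBP and using a contraceptive method that is highly effective (with a failure rate of <1% per year), with high user dependency", with a second effective method added.
- **10.4.3** fixes who leaves the WOCBP class. On menopause it says: "A postmenopausal state is defined as no menses for 12 months without an alternative medical cause". A later sentence covers women on HRT whose menopausal status is in doubt. They must use non-oestrogen hormonal contraception "if they wish to continue their HRT during the study".
- **10.4.4** lists eight highly effective methods. Item 6, in the user-dependent group, is "Combined (estrogen and progestogen-containing) hormonal contraception associated with inhibition of ovulation", by oral, intravaginal or transdermal route. The qualifiers on it are approval status in Japan and the barrier method required for all user-dependent methods.
- **5.3.2** has the investigator, together with the participant, confirm that she "has selected an appropriate method of contraception for the individual participant and his or her partner(s) from the permitted list of contraception methods". The contraception-check footnote to Table 1 of the Schedule of Activities adds: "The investigator or designee will inform the participant of the need to use highly effective contraception consistently and correctly".

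**The concern.** Inclusion 6 exists to remove ovarian oestrogen in women with ER+ disease. Appendix 4 uses a general contraception list that offers the same women a product containing oestrogen. The protocol's own rationale makes the mismatch plain: 2.2.6 describes fulvestrant as an ER antagonist, and 4.2.2 says that KAT6A promotes ER+ breast cancer growth through ER signalling. An ER+ participant who started or stayed on a combined product would be within the contraception list while counteracting treatment that the protocol requires or tests.

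What is at stake is the individual participant's treatment and the consistency of the instructions that sites follow. Nothing in the design, the decision rules or the analysis depends on it.

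**Working it through.** No formula or power figure is involved, so the check sets the provisions side by side and then counts.

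**Step 1. Does the agonist take an ER+ woman out of the WOCBP class?** No. Inclusion 7 places every ER+ woman who does not meet its criteria in that class. Under 10.4.3 a woman stays fertile until postmenopausal unless permanently sterile. Amenorrhoea produced by an LHRH agonist has a medical cause, namely the drug, so it does not satisfy "A postmenopausal state is defined as no menses for 12 months without an alternative medical cause", and it is not permanent sterility.

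**Step 2. Does the agonist itself serve as her contraceptive?** No. It is not among the eight methods in 10.4.4. She must still pick one, as 5.3.2 and the Schedule of Activities footnote require.

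**Step 3. Is the list limited by tumour type or ER status?** Not in 10.4.2, 10.4.4 or 5.3.2. The one general limit in 10.4.4 is local availability and regulation. The only wording about non-oestrogen contraception in readable Appendix 4 is the HRT sentence in 10.4.3, which concerns doubtful menopausal status and does not mention ER+ disease.

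**Step 4. Which methods are listed?**

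| Type | Items | Count |
|---|---|---|
| Combined oestrogen-progestogen | 6 | 1 |
| Progestogen-only or hormone-releasing | 1, 3, 7 | 3 |
| Non-hormonal: intrauterine device, bilateral tubal occlusion, vasectomised partner, abstinence | 2, 4, 5, 8 | 4 |
| Total | | 8 |

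Without item 6, 8 − 1 = 7 remain. Without items 1, 3 and 7 as well, 7 − 3 = 4 remain.

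**Step 5. Whom can item 6 reach?** Section 2.2.4 gives the participants treated by 12 September 2022.

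| Part | Treated | ER+HER2- breast cancer |
|---|---|---|
| 1A | 21 | 9 |
| 1B | 4 | 4 |
| 2A | 33 | 33 |
| 2B | 8 | 8 |
| Total | 66 | 54 |

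54/66 = 81.8%. The other 66 − 54 = 12 were 10 with CRPC and 2 with NSCLC, so at most 2 treated women had disease other than ER+ breast cancer. The protocol does not say how many of the 54 were of childbearing potential. Many may have qualified under inclusion 7, so the possible range is 0 to 54.

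**The case against.** The strongest reply is that this is a standard list of options and that no participant is told to use item 6. That stands. A reader might infer that inclusion 6 and 10.4.4 contradict each other. They do not: a woman can accept the agonist and choose any of the other seven methods.

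The second reply is that safeguards already exist. Section 5.3.2 asks for a method appropriate to the individual, confirmed by the investigator; 10.4.2 prefers low user dependency, and item 6 is user dependent; 6.5.2 sends sites to product labels for prohibited medications. These make use unlikely, and the point is graded accordingly. None of them names oestrogen in the readable text, and the list itself states the opposite permission.

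The third reply is redaction. Most of exclusions 18 to 25, section 5.3.1, much of 6.5.1 to 6.5.3 and the tables of Appendices 14 and 15 are blacked out. A reader might infer that the protocol contains no restriction on oestrogen; the documents cannot show that. What can be said is that 10.4.4 is readable and points to no such restriction. If one exists, only a missing cross-reference remains.

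A reader might also see a sharper problem in Japan, where item 1 and both forms of item 7 are marked as not approved, leaving the oral combined pill as the only systemic hormonal method. That adds nothing, because no systemic hormonal method is ever required and the four non-hormonal methods are all still listed there.

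Finally, the HRT sentence in 10.4.3 belongs to the rule for establishing menopausal status and waives neither inclusion 6 nor inclusion 7. It is at most an optional clarification.

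**Conclusion.** The point holds as a minor matter of participant safety and consistency. The list in 10.4.4 permits combined oestrogen-progestogen contraception to any WOCBP with no exception for ER+ breast cancer, although inclusion 6 asks ER+ women of childbearing potential to accept induced menopause.

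The frequency is expected to be low. No affected participant is shown, and the range of 0 to 54 is a bound and not an estimate. A reader might infer an effect on response rates or on the dose-limiting toxicity assessment; nothing in the documents supports one, and none is claimed.

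The conclusion rests on two assumptions: that a woman on an LHRH agonist remains a WOCBP under 10.4.3, which follows from its wording, and that no redacted passage already restricts oestrogen, which cannot be checked. If the second fails, the finding shrinks to an alignment of text.

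**What to change.** - **In 10.4.4**, add one sentence: participants with ER+ breast cancer may not use oestrogen-containing contraception (item 6) and should use a listed non-hormonal method. The sponsor's clinical team should rule on the progestogen methods (items 1, 3 and 7).
- **Keep the general list** for participants with NSCLC and for partners of male participants, for whom item 6 raises no such conflict.
- **Optionally, in 10.4.3**, state that the HRT-continuation sentence does not apply to participants with ER+ breast cancer.
- **If redacted text or the product labels already restrict oestrogen**, refer to that restriction from 10.4.4 instead of writing a new rule.

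The cost is one sentence, or two with the HRT clarification, and a consistency check against 6.5. ER+ participants keep seven of the eight methods, or four if every hormonal method is excluded. No visit, assessment, sample size or analysis changes.

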## 10.5. Appendix 5: Genetics

### Use/Analysis of DNA

- Genetic variation may impact a participant's response to study intervention, susceptibility to, and severity and progression of disease. Therefore, where local regulations and IRBs/Ecs allow, a blood sample will be collected for DNA analysis.
- The scope of the genetic research may be narrow (eg, 1 or more candidate genes) or broad (eg, the entire genome), as appropriate to the scientific question under investigation.
- The samples may be analyzed as part of a multistudy assessment of genetic factors involved in the response to PF-07248144 [REDACTED]  
[REDACTED]
- The results of genetic analyses may be reported in the CSR or in a separate study summary, or may be used for internal decision making without being included in a study report.
- The sponsor will store the DNA samples in a secure storage space with adequate measures to protect confidentiality.
- The samples will be retained as indicated:
  - Samples for specified genetic analysis (see [Section 8.7.1](#)) for a period of up to 3 years after regulatory approval.
  - Samples for banking (see [Section 8.7.2](#)) will be stored indefinitely or for another period as per local requirements.
- Participants may withdraw their consent for the storage and/or use of their Banked Biospecimens at any time by making a request to the investigator; in this case, any remaining material will be destroyed. Data already generated from the samples will be retained to protect the integrity of existing analyses.
- Banked Biospecimens will be labeled with a code. The key between the code and the participant's personally identifying information (eg, name, address) will be held at the study site and will not be provided to the sample bank.

